## **2.11 Will health service research issues be addressed?**

Our study addresses health service research issues from the point of view of HCP contamination and safety, as well as clinical care of COVID-19 patient using new technology. No additional health service research issues will be addressed.

## **2.12 Are there likely to be any problems with compliance?**

There is a possibility that participants recruited to the intervention arm (i.e. aerosol box) will struggle with performing the airway procedure, which may in turn influence their effort to complete the required task. All participants recruited to the intervention arm will receive comprehensive training, including an opportunity to practice airway procedures with an aerosol box coupled with expert feedback. We will implement a multifaceted approach to ensure compliance with our research protocol

across recruitment sites: (1) development of standard operating procedures and a research protocol guide; (2) submission of recordings of at least one pilot session per site, which will be reviewed by the principal investigator for protocol adherence before recruitment commences; (3) submission of a videotaped recording of one recruitment session per site, three months into the study. Videos will be reviewed by the principal investigator for protocol adherence, with feedback provided to site investigators. We don't anticipate any additional issues with protocol compliance or completion of tasks.

### **2.13 *Loss to follow-up.***

This is not applicable as we are not planning any follow-up.

### **2.45 *Recruitment Centers.***

Securing space to recruit for simulation-based studies has become more challenging due to institutional restrictions imposed as a result of the COVID-19 pandemic. To overcome this issue and to ensure our study is completed in a timely fashion, the study will be implemented at four INSPIRE network sites (Alberta Children's Hospital, Ste. Justine Hospital, and Children's Hospital of Los Angeles and The Hospital for Sick Children).

### **2.16, 2.17 *Statistical analysis.***

Demographic characteristics of participants including sex, profession, years of clinical experience and other identifiers (e.g. height, body surface area) will be reported using descriptive statistics between 2 study arms. For the primary outcome, assuming non-normal distribution of data, we will use Wilcoxon rank sum tests to compare the AOC in 3 different procedures in both airway providers and assistant roles. Analyses to evaluate the degree of contamination pre- and post-doffing of PPE will be conducted separately. Time to procedural completion and first pass success rates will be compared with the Wilcoxon rank sum tests.

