### 1.2 Principal research questions.

The primary aim of this study is to evaluate the effectiveness of aerosol box use, compared with no aerosol box use, for reducing HCP contamination during performance of AGMPs by a trained airway team during care of a simulated patients in respiratory failure due to COVID-19. We hypothesize that the use of an aerosol box, compared with no aerosol box use, will reduce HCP contamination caused by AGMPs during care of simulated patients in respiratory failure due to COVID-19.

The secondary aim is to determine if aerosol box use influences the time to successful completion and first-pass success rate for ETI and LMA insertion in trained airway teams. We hypothesize that there will be no significant differences in time to ETI and LMA insertion and first pass success rates when comparing airways teams using an aerosol box with teams not using an aerosol box.

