## **2.8, 2.9 Outcome measures.**

Primary outcome: Surface area of contamination (AOC) quantified from digital photos of GloGerm™ deposited on the airway team members pre and post-doffing. A digital reference grid will be applied over each photo, with mean grey values of areas within each grid “pixel” calculated using Image J (NIH) software. As areas highlighted by GloGerm™ will illuminate more brightly, mean grey value per pixel will be the base unit to quantify degree of contamination relative to the provider’s anatomic surface area. This quantitative measure permits comparative analysis between groups or scenarios, and is congruent with accepted measures in the bioimaging informatics, digital immunohistochemistry, and direct immunofluorescence. Digital images of participants will be captured in a standardized fashion under UV-illumination in a fashion to minimize confounders (brightness, angle, lighting) (see budget). Images will be taken pre- and post-doffing to capture extent of contamination on PPE (pre) and extent of contamination on provider surfaces underneath PPE.

Secondary outcomes: (a) time to successful intubation or LMA insertion (captured by video review by 2 trained and calibrated raters); (b) first pass success rate for ETI and LMA insertion (captured by video review by 2 trained and calibrated raters).

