## **2.10 Sample size.**

Sample size estimation is based on primary outcome measure. Given the paucity of quantitative research in this area, we propose a sample of 60 teams (120 participants) in total, or 30 teams (60 participants) per study arm. As each team will receive repeated measures (i.e. 3 scenarios), this sample size allows us to detect a medium effect size (Cohen’s  $d = 0.65$ ), with a significance level of 0.05, a power of 0.8, and a high intra-cluster correlation coefficient ( $\rho = 0.7$ ) to make a conservative estimation. Accounting for missing data due to technical issues, we will recruit 2 extra teams per study group, resulting in a total sample size of 64 teams (128 participants).

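### The primary outcome is split into 12 rank-sum tests with none named as decisive, and the combined three-scenario comparison that the sample size powers is never run

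*Protocol*

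**What the plan says.** Section 1.2 states one directional hypothesis: box use, compared with no box, "will reduce HCP contamination caused by AGMPs during care of simulated patients in respiratory failure due to COVID-19".

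Sections 2.8, 2.9 define the primary outcome as the contaminated surface area (AOC), "quantified from digital photos of GloGerm™ deposited on the airway team members pre and post-doffing". No role, procedure or time point is put first.

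Sections 2.16, 2.17 give the primary analysis: "we will use Wilcoxon rank sum tests to compare the AOC in 3 different procedures in both airway providers and assistant roles". They add: "Analyses to evaluate the degree of contamination pre- and post-doffing of PPE will be conducted separately". No pooled test is described, and no significance level is attached to these tests.

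Section 2.10 sizes the trial on the primary outcome: 30 teams per arm, three scenarios per team as repeated measures, Cohen's d of 0.65, "with a significance level of 0.05, a power of 0.8, and a high intra-cluster correlation coefficient" of 0.7. Two extra teams per arm allow for missing data, giving 64 teams in total.

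The only model that could combine scenarios is the mixed-effects regression in section 2.18. It is a secondary analysis of factors other than the box.

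**The concern.** Sections 1.2 and 2.10 each describe one question at one level of 0.05. The analysis section answers it with 12 results and does not say which of them, or how many, would support the hypothesis. A mixed pattern is easy to imagine: less contamination of the airway provider during bag-valve-mask ventilation only, or a difference before doffing but not after. The protocol gives no way to decide whether that confirms the hypothesis, so the choice could be made after the data are seen. Section 1.4 expects the results to inform clinical practice, institutional airway policy and PPE protocols, so the choice matters.

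The second problem is one of fit. The comparison that was powered is not in the analysis, and the comparisons in the analysis do not have the stated power.

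**Working it through.** **Inputs.** From section 2.10: d = 0.65, significance level 0.05 (sidedness not stated; two-sided reproduces the sample size), power 0.8, correlation 0.7, three scenarios, 30 teams per arm. From sections 2.16, 2.17: three procedures, two roles, two separate time points. Not given: the correlations between roles and between pre- and post-doffing. These are assumed to lie between 0 and 0.7, with 0.9 as an extreme.

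**1. The plan's own sample size.**
- One measure per team: n per arm = 2 x ((1.960 + 0.842)/0.65)^2 = 37.15.
- Mean of three scenarios with correlation 0.7: variance factor (1 + 2 x 0.7)/3 = 0.80, so SD = 0.894 and n = 37.15 x 0.80 = 29.7, rounded up to 30. This matches the protocol.
- Six measures per team (three scenarios x two members) at the same correlation: factor (1 + 5 x 0.7)/6 = 0.75, n = 27.9, or 28. The stated 30 therefore fits one value per team per scenario, combined over three scenarios.

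**2. Power with 30 teams per arm, d = 0.65, two-sided 0.05.**
- Team mean over three scenarios: sqrt(30/2) x 0.65/0.894 = 2.815; 2.815 - 1.960 = 0.855; power 0.804 (t-test 0.790).
- One scenario, as the analysis section plans: sqrt(30/2) x 0.65 = 2.517; 2.517 - 1.960 = 0.557; power 0.711 (t-test 0.697).

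**3. Number of primary tests.** 3 x 2 x 2 = 12.

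**4. Chance of at least one p < 0.05 among 12 tests when the box has no effect.** Independent tests: 1 - 0.95^12 = 0.460. The correlated cases come from multivariate normal simulation (500,000 to 1,000,000 draws).

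| Correlation among the 12 tests | Either direction | In the box's favour |
|---|---|---|
| Independent | 46.0% | 26.2% |
| 0.7 across scenarios; roles and time points independent | 37.0% | 20.2% |
| Common 0.5 | 31.9% | 16.0% |
| 0.7 multiplying across scenario, role and time | 27.8% | 13.9% |
| Common 0.7 | 23.2% | 11.6% |
| Common 0.9 (extreme) | 13.5% | 6.8% |

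The nominal values are 5% and 2.5%. A direct simulation of rank-sum tests with 30 teams per arm (4,000 runs) gave 23.9% and 11.9% at a common 0.7, close to the normal approximation.

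**5. Keeping all 12 tests with a Bonferroni correction.** The level per test is 0.05/12 = 0.0042. Power of a single-scenario test falls from about 0.70 to 0.36 (normal), 0.33 (t-test) or 0.31 (rank-sum).

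**The case against.** The strongest reply is that the protocol nowhere says one significant result out of 12 counts as success. It does not write the number 12, and it gives 0.05 only in the sample-size section. Multiplicity rules and testing order are commonly left to a statistical analysis plan, which is not shown here. This stands. A reader might infer that the trial has a 28-46% chance of a false primary claim, but the documents do not support that. The figure needs a success rule that they do not contain. Its lower end needs 0.7 to multiply across scenario, role and time; using 0.7 as one common correlation gives about 23%. It also counts results against the box, although the hypothesis concerns a reduction only.

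A second reply is that procedure-specific results are wanted: section 1.1 aims to describe contamination patterns after each procedure, and section 2.2 sets up comparisons between procedures. That is a fair reason to report them, but not to leave the overall hypothesis without a test.

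The reply does not reach the mismatch. The protocol itself chooses the split into procedures, roles and time points, and that choice differs from the comparison in section 2.10. An analysis plan could repair this only by adding a test that the protocol's analysis section does not contain.

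**Conclusion.** The point holds as a mismatch within the protocol. One hypothesis is met by 12 rank-sum tests, none decisive, and the combined comparison behind the sample size is absent. The missing multiplicity adjustment is not by itself the finding.

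A single-scenario test has power of about 0.70, against the stated 0.80. This takes d = 0.65 as the standardised effect in one scenario, the reading that reproduces 30 teams per arm.

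The error rate is conditional. If any one of the 12 two-sided tests at 0.05 were read as success, the false-positive chance would be about 23-46%, and about 12-26% for a false claim in the box's favour. The range runs from a common correlation of 0.7 to independence. A common 0.9 would lower the figures to 13.5% and 6.8%, still above nominal. The exact figure cannot be fixed from the document; the direction does not depend on it.

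**What to change.** Name one primary test at two-sided 0.05 on one AOC value per team, combined over the three scenarios and both team members at one named time point, for example pre-doffing. State how a missing scenario value is handled: the mean of the available scenarios, or a mixed model. Section 2.10 already expects some missing data.

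Then test in fixed order, each only if the one before is significant:
1. the same team measure at the other time point;
2. the airway provider, at the primary time point;
3. the airway assistant, at the primary time point.

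Report the procedure-specific comparisons with confidence intervals, as descriptive results.

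This uses the comparison that section 2.10 powers at about 0.80, and it is cheaper than correcting all 12 tests. It needs wording only, made before the data are analysed, with no extra teams or measurements. The price is that procedure-specific contrasts lose formal primary status. Which time point comes first is for the investigators to choose, but the choice must be written down.

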### **2.18 *Subgroup analysis.***

Although stratifying by sex during randomization will ensure equal distribution of different sex in both groups, the physical stature of each provider may be a factor that influences the extent of contamination. We will conduct secondary analysis to explore if factors other than aerosol box (i.e. sex, body surface area, number of years clinical experience of the airway expert, experience of doing multiple procedures within incubator) will influence the degree of contamination, time to successful intubation and LMA insertion, and first pass success rate for ETI and LMA insertion using mixed-effect linear regression model. The similar secondary analyses focusing on the degree of contamination of the airway assistant will be performed as well while stratified by these factors.

### **2.19 *Has any pilot study been carried out using this design?***

Pilot studies conducted by [name] have established the feasibility of using Glo-Germ™ and the respiratory airway manikin for simulating aerosolization and droplet spray during AGMPs. [name] team has developed aerosol box training videos (and training protocols), and pilot tested the use of the aerosol box and simulated cough to aerosolize Glo-Germ. Preliminary data (unpublished) demonstrates minimal contamination of HCPs and the environment with use of the aerosol box (<https://www.youtube.com/watch?v=obABuAqFcd4&feature=youtu.be>).

